## Background

Chronic obstructive pulmonary disease (COPD) is characterised by exertional dyspnoea, reduced exercise tolerance, marked disability and frequent hospitalisation. The current economic burden of COPD to the health system is considerable, with the majority of costs attributable to hospital use
[1,2]. International guidelines for managing COPD include referral to pulmonary rehabilitation
[3], supported by compelling evidence that such programs deliver improvement in exercise capacity, reduction in breathlessness and improvement in health-related quality of life (HRQOL), irrespective of disease severity
[4]. Pulmonary rehabilitation is also associated with a reduced frequency of acute exacerbations and hospital admissions
[5]. Despite the strong evidence of its benefits, the proportion of people with COPD who receive pulmonary rehabilitation is very small, with estimates from developed countries suggesting that it is delivered to less than 5% of those who would benefit each year
[6,7]. Of those people with COPD who are referred to pulmonary rehabilitation, 8% to 50% will never attend
[8,9], while non-completion rates range from 10% to 32%
[10,11]. The practical reasons for this lack of access include a shortage of programs, particularly in rural and regional centres, and an insufficient number of qualified health professionals. Patient-related barriers to attendance have also been identified, with travel and transport to centre-based programs being the most common obstacles to attendance in this disabled group
[8,10-16].

In view of these barriers, the current model of a centre-based pulmonary rehabilitation program is not addressing the needs of many people with COPD who would benefit from this intervention. If new models are not found, uptake of these programs by patients with COPD will continue to be limited. Home-based, unsupervised pulmonary rehabilitation has been proposed as an alternative model which may enhance access and uptake while containing the rising costs of healthcare associated with COPD
[17-20]. Direct comparison of home and centre-based pulmonary rehabilitation has been explored in four studies
[17-20]. Home-based programs were found to be safe, with improvement in exercise tolerance and HRQOL and reduced symptoms demonstrated in both the home and hospital-based groups. However, only one study was a non-inferiority trial

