There is a need for new models of pulmonary rehabilitation which allow all program components to be delivered at home, with proven clinical outcomes and low costs. The aims of this study are to 1) compare completion rates of a home-based self-monitored pulmonary rehabilitation program with a hospital-based, outpatient program in people with COPD; 2) compare the clinical benefits of home-based pulmonary rehabilitation and hospital-based pulmonary rehabilitation and 3) compare the costs of home-based and hospital-based pulmonary rehabilitation. We hypothesise that the proportion of patients who complete pulmonary rehabilitation will be greater in the home-based intervention; the clinical effects on exercise capacity, symptoms and quality of life will be equivalent in both models; and the home-based program will be more cost-effective.

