### Analysis

Continuous variables will be examined with repeated measures analysis of variance and linear mixed models, as appropriate. The proportion of participants who complete the program will be compared between groups using a chi-squared test and the relative risk of non-completion will be determined. All data will be analysed by intention to treat. A per-protocol analysis will also be conducted to reduce the risk of Type 1 error, as recommended in the CONSORT Extension for reporting of non-inferiority and equivalence trials
[48]. Alpha will be set at 0.05.

Sample size calculations are based on the primary outcome of change in 6MWD. If there is truly no difference in the change in 6MWD between home-based and hospital based groups, then 144 participants are required to be 80% sure that the 95% confidence interval will exclude a difference in means of more than 25 metres. We have recently demonstrated that this is the minimal important difference for 6MWD in our population of patients with COPD
[49]. This assumes a standard deviation of the change in 6MWD of 51 metres
[50]. On the basis of our previous trials in pulmonary rehabilitation
[49,50], we expect 15% attrition from the study; we will therefore randomize a total of 166 participants.

This sample size will also provide appropriate power for the secondary outcomes:

***Completion:*** Data from our centres indicate that only 66% people who are referred to pulmonary rehabilitation take up the referral and complete the centre-based program. Previous studies have documented very high completion rates for home-based programs of over 90%
[18]. Using a more conservative estimate of 85% completion, 144 patients will be required to detect a difference in completion rates between hospital and home-based groups (72 in each group).

***Dyspnoea:*** If there is truly no difference in the change in the dyspnoea domain of the CRQ between home-based and hospital based groups, then 142 participants are required to be 80% sure that the 95% confidence interval will exclude a difference in means of more than 2.5 points. This is the minimal important difference for the dyspnoea domain of the CRQ
[51] and assumes a standard deviation of the change in CRQ dyspnoea of 5.1 points
[50].

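### The completion calculation asks for too few participants for 80% power, and its 66% hospital rate counts people referred, not people randomised

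*Protocol article*

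**What the plan says.** The Background makes completion the first aim, with a directional hypothesis that "the proportion of patients who complete pulmonary rehabilitation will be greater in the home-based intervention". Outcome measures defines completion as at least 70% of planned sessions. Under Analysis, completion is to be "compared between groups using a chi-squared test", with the relative risk of non-completion reported. The same section says "Alpha will be set at 0.05" and that all data are analysed by intention to treat.

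The sample size is set by 6-minute walk distance: 144 participants, raised to 166 for 15% attrition. The article then says "This sample size will also provide appropriate power for the secondary outcomes". For completion, the hospital rate comes from the centres' own data: "only 66% people who are referred to pulmonary rehabilitation take up the referral and complete the centre-based program". The home rate is 85%, described as more cautious than published rates of over 90%. The conclusion is that "144 patients will be required to detect a difference in completion rates between hospital and home-based groups (72 in each group". No power percentage and no sidedness are given for this outcome. The 6-minute walk and dyspnoea calculations both state 80%.

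The Background reports two losses after referral separately: 8% to 50% never attend, "while non-completion rates range from 10% to 32" per cent. Recruitment and randomisation says that consent is obtained and that allocation follows the baseline assessment.

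**The concern.** Two things look wrong.

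First, 72 per group is smaller than the usual two-sided calculation gives for these rates at 80% power, and 144 is the same total as for the walk distance.

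Second, the two rates do not describe the same kind of population. The hospital figure is a share of everyone referred, including those who never started. The trial's denominator is people who agreed to take part and came for baseline testing. If the hospital rate in that group is higher, the assumed 19-point gap is too wide and the true power is lower than the article implies.

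Completion is aim 1, and access is the reason for the trial. A reader told that power is adequate could take a non-significant result as evidence that the programs are completed equally often.

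**Working it through.** **Inputs.** Hospital p1 = 0.66, home p2 = 0.85, alpha 0.05, chi-squared test, 72 per group, 166 randomised (83 per group at 1:1), all from Analysis. Assumed because not stated for completion: a two-sided test, no continuity correction, and 80% power as in the other two calculations.

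**Step 1: the article's figure.** With p̄ = 0.755,

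n per group = [1.96·√(2·0.755·0.245) + 0.8416·√(0.66·0.34 + 0.85·0.15)]² / 0.19²
= [1.96·0.6082 + 0.8416·0.5932]² / 0.0361 = 79.2, so 80 per group (160 in total).

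Other two-sided forms at 80% power give 77 (unpooled), 78 (arcsine) and 90 (continuity-corrected). None gives 72. Two routes come close: a one-sided 5% test with continuity correction (72.5, so 73 per group), and a two-sided test at 75% power (70.2, so 71 per group). The article states neither.

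**Step 2: power at the stated rates, two-sided.**
- 72 per group, normal approximation: z = [0.19·√72 − 1.96·0.6082] / 0.5932 = 0.708, power 76.1%. Exact enumeration of the uncorrected test gives 77.4%.
- 83 per group: z = [0.19·√83 − 1.96·0.6082] / 0.5932 = 0.908, power 81.8%. Exact 82.6%.
- With a Yates-corrected test the exact values are 70.2% and 77.5%.

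**Step 3: the hospital rate.** The 66% is a product: share taking up × share of those completing. If 8% never attend (the low end of the Background range, assumed here for these centres), completion among those who start is 0.66/0.92 = 71.7%. Read as completion among starters, the Background's 10% to 32% non-completion means 68% to 90% completion. Neither figure is the rate among randomised people. They show the direction and a plausible range.

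**Step 4: power over that range.** Exact power, two-sided uncorrected chi-squared test, 83 per group:

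| Hospital completion | Home 85% | Home 90% |
|---|---|---|
| 66% | 83% | 97% |
| 68% | 75% | 95% |
| 70% | 65% | 91% |
| 75% | 37% | 74% |
| 80% | 14% | 44% |

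At 71.7% hospital and 85% home, power is 56%. With home at 85%, power drops below one half just above 72.5% hospital completion.

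**The case against.** The best defence is that the article promises no particular power for completion. The 80% benchmark is borrowed from neighbouring sentences, and against it 72 per group falls short by only 3 to 4 points. Stopping the program is itself the outcome, so attrition need not shrink the denominator: by intention to treat all 166 count, and at the stated rates power then exceeds 80%. This stands. A reader might infer that the power claim fails outright, but at 66% v 85% it does not; what is wrong is the number said to be required.

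A reader might also infer that people who would not take up a referral cannot be in the trial. The article does not support that. Recruitment takes place at respiratory clinics, at referral and from program databases, and randomisation precedes the program. Someone allocated to hospital who never attends stays in the analysis as a non-completer. Consent and a baseline visit make this less common than among all referrals, but the article does not say by how much. The Background sentence also gives no explicit denominator for its 10% to 32%, and its lowest implied completion rate, 68%, is only two points above 66%.

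Nor is a non-significant result shown to be likely. That needs hospital completion above about 72.5% with home held at 85%. The article treats 85% as cautious, and at 90% power is much better. Finally, completion is not the only superiority hypothesis, because the home program is also expected to be more cost-effective.

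What survives is that the hospital rate is measured on a different denominator from the trial's, with no adjustment or caveat.

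**Conclusion.** The point holds in limited form. The requirement of 144 is too low for 80% power with a two-sided 5% chi-squared test: about 160 are needed, and 72 per group gives about 76-77%. The planned 166, all analysed, gives about 82-83% without continuity correction, so the arithmetic slip alone does little harm.

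The more important weakness is that adequate power is claimed from a referral-based hospital rate. Among randomised participants the rate is likely to be higher. With home completion at 85%, every hospital rate from 68% to 80% gives less than 80% power; with home completion at 90%, power stays above 80% at 68% and 70% but not at 75%. The statement about adequate power is therefore conditional on rates the article does not justify for its own population. The results assume equal allocation, completion status known for everyone randomised, and a two-sided uncorrected test.

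**What to change.** In the Completion paragraph:

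- Replace the statement that 144 (72 per group) are required with the power for all 166 randomised by intention to treat: about 82-83% at 66% v 85%, two-sided 5%, uncorrected chi-squared. State the sidedness and whether a continuity correction is used.
- Say that 66% is a rate among people referred and that completion among randomised participants may be higher.
- Give power over a range of hospital rates, for example 68% to 80%, at home rates of 85% and 90%.
- Limit the claim of adequate power to the combinations where it holds.

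A 95% confidence interval for the risk difference could be reported beside the planned relative risk, so that a non-significant result is read by its width. This is an option; the planned measure is acceptable.

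The cost is a less favourable stated power. No patients, visits or analyses of the primary outcome change.

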## Discussion

This research will be the first study comparing both the clinical effects and cost effectiveness of delivering pulmonary rehabilitation in the home and hospital settings. With the substantial morbidity and mortality associated with COPD
[2], and the growing proportion of people with COPD, there is an increasing need for cost effective treatment strategies. Pulmonary rehabilitation is a low-cost, vital component of both short and long term management of COPD
[3,29]. Currently, the most common method of delivering pulmonary rehabilitation is a centre-based approach, which may be accomplished within an outpatient hospital department, community centre or private practice
[52]. The lack of access to this intervention for a significant proportion of people with COPD is likely to be a contributing factor to the patterns of decline in exercise capacity and increase in symptoms characteristic of this disease
[3]. In comparing the two modes of delivery on important clinical features and the economic impact to both the patient and the healthcare system, further information on the feasibility of a home-based model of pulmonary rehabilitation will be obtained.

It has been well documented that the effects of pulmonary rehabilitation, including those conducted via a centre-based approach, diminish over time, with deterioration in both exercise capacity and HRQOL within 6 to 12 months of program completion
[53]. One key reason for this decline may be the difficulty in maintaining regular exercise routines and adherence over the longer term
[53]. A critical goal of pulmonary rehabilitation is to both maximize and sustain benefits. It is possible that undertaking pulmonary rehabilitation within the home environment may promote more effective integration of exercise routines into daily life over the longer term. With greater adherence to exercise, the initial benefits of pulmonary rehabilitation may be better maintained.

The results of this study will inform guidelines for the provision of pulmonary rehabilitation in COPD and may have a significant impact on the delivery of healthcare to people with COPD. If it is demonstrated that home-based exercise achieves equivalent clinical outcomes and is cost effective compared to a hospital-based program, this increases the options for the provision of this intervention and may assist in overcoming the most frequently identified barriers to pulmonary rehabilitation.

### Trial status

Patient recruitment commenced in October 2011 and is continuing.

## Abbreviations

COPD: Chronic obstructive pulmonary disease; QALYs: Quality-adjusted life years; FEV1: Forced expiratory volume in one second; FVC: Forced vital capacity; 6MWT: 6-minute walk test; 6MWD: 6-minute walk distance; HRQOL: Health-related quality of life; SF-36: Short form-36; PRAISE: Pulmonary rehabilitation adapted index of self-efficacy; HADS: Hospital Anxiety and Depression Scale; MBS: Medicare Benefits Scheme; PBS: Pharmaceutical Benefits Scheme; SF-6D: Short form-6.
